**Fig. 2 Fig2:**
[figure not shown]
Flow chart of study outline

Suitable eligible patients will be screened for study participation and begin the consenting process, where the study objectives and the risks and benefits of participating are explained to them. Informed consent forms for the study will be filled out by subjects to confirm enrollment and they will undergo a baseline assessment, including a thorough neurological and neuropsychiatric examination, as well as standardized subjective and objective gait assessments. The Columbia Suicide Severity Rating Scale is included during screening given the known risk of suicidality with DBS for PD [51]. After enrolment and baseline evaluation, subjects will be consented for surgery prior to bilateral implantation of DBS electrodes in the CnF, with a post-operative CT scan to localize final electrode positions. For ethical reasons, all subjects will receive active stimulation beginning at 2 weeks post-implantation and will undergo repeated gait assessments in the clinic at 2-, 6-, 12-, and 24-weeks post implantation (Table 1). Gait assessment tests will be performed on medication, with DBS on and off, and assessors will be blinded to whether the DBS is on or off to minimize the risk of bias. A more detailed kinematics and EMG gait assessment, using the Nexus system (Vicon Motion Systems Ltd) will take place at study onset and conclusion. At study conclusion, subjects will decide whether they want to continue with stimulation or discontinue stimulation; in both cases, they will continue to receive their usual standard care and follow up with their neurologist.

**Table 1 Tab1:** Detailed study schedule

Assessment	Visit 1	Visit 2	Visit 3	Visit 4	Visit 5	Visit 6	Visit 7	Visit 8	Visit 9
	Screen	Baseline assessment	Surgical screening	Surgery	2-week F/U	6-week F/U	12-week F/U	24-week F/U	25-week F/U
**Screening ICF**	X								
**Pre-op work up**^*^ **(CBC, CMP, β-hCG, INR/PTT/PT, U/A, EKG, CXR)**	X		X						
**Neuropsychiatric evaluation (including MDRS and BDI)**	X	X	X		X	X	X	X	
**Columbia Suicide Severity Rating Scale**	X	X	X		X	X	X	X	
**Gait assessment**	X	X			X	X	X	X	
**MDS-UPDRS**	X	X			X	X	X	X	
**FOG Questionnaire**		X			X	X	X	X	
**Timed Up and Go test**		X			X	X	X	X	
**Velocity test**		X			X	X	X	X	
**Variability test**		X			X	X	X	X	
**PDQ-39**		X	X		X	X	X	X	
**PDQL**		X	X		X	X	X	X	
**Brief pain history and NPSI**		X	X		X	X	X	X	
**Surgical ICF**			X						
**MRI**			X						
**Device implantation**				X					

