### Kinematic and EMG evaluation of gait

Lower-limb gait kinematics and EMG will be evaluated with and without DBS in study subjects (*n* = 4). Subjects will be fitted with fifteen reflective markers that will be tracked at 100 Hz with a 10-camera Nexus system (Vicon Motion Systems Ltd) attached bilaterally to the first and fifth distal phalange of the foot, lateral malleolus, calcaneus, lateral femoral epicondyle, anterior superior iliac spine, and the mid-shank and mid-thigh. A reflective marker will also be placed on the lower back region overlying the sacrum. EMG surface electrodes will be placed over the tibialis anterior (TA) as well as the lateral gastrocnemius (LG). Subjects will be asked to walk along a 25-foot path at a constant, regular walking pace both without and then with optimal DBS configuration settings (CnF L on/CnF R on), DBS OFF (CnF L off/CnF R off), DBS RIGHT Only (CnF L off/CnF R on), and DBS LEFT only (CnF L on/CnF R off) repeating each condition twice. Kinematic and EMG signals will be recorded during each trial while the subjects walk for 25 ft. and averaged for each test condition.

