### Data analysis

The primary goal of this pilot study is to assess the safety and feasibility of delivering DBS to the CnF in PD patients with refractory FOG and thus will only involve 4 subjects. We believe this number of subjects will provide adequate data on safety and feasibility for a larger study. However, assessment of trend toward efficacy will be performed for the secondary outcomes. One-way ANOVA will be used to compare percent improvement in gait velocity for the four different DBS configurations (L CnF off/R CnF off, L CnF off/R CnF on, L CnF on/R CnF off, L CnF on/R CnF on) at each clinic visit, with the Tukey Honest Significant Difference post hoc test to compare configurations. The same test will be used to compare changes in EMG amplitude between the four DBS configurations at the final gait assessment at the study’s conclusion. One-way ANOVA with repeated measures will be used to compare changes in the UPDRS III, FOG Questionnaire, PDQ-39, and PDQL over the multiple time points of the study.

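### The four-configuration velocity ANOVA is planned for every clinic visit, but the clinic assessments are described only as DBS on and off

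*Protocol article*

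**What the plan says.** All references are to the protocol article.

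- **Data analysis, velocity.** "One-way ANOVA will be used to compare percent improvement in gait velocity for the four different DBS configurations": both sides off, right only, left only, both on. The list of configurations closes with "L CnF on/R CnF on) at each clinic visit". The timing and follow-up test are "at each clinic visit, with the Tukey Honest Significant Difference post hoc test to compare configurations".
- **Data analysis, EMG.** The next sentence uses the same test to "compare changes in EMG amplitude between the four DBS configurations at the final gait assessment at the study’s conclusion". Velocity and EMG are thus given different timings.
- **Study design and overview (text after Fig. 2).** Patients "will undergo repeated gait assessments in the clinic at 2-, 6-, 12-, and 24-weeks post implantation". Of these assessments it says: "Gait assessment tests will be performed on medication, with DBS on and off". Blinding is framed in the same two states: "assessors will be blinded to whether the DBS is on or off".
- **Assessments.** Clinic velocity is an average over a 2-minute walk. No unilateral condition is named.
- **Secondary outcomes.** The velocity outcome is a percent change with versus without CnF stimulation.
- **Kinematic and EMG evaluation of gait.** Here, and only here, unilateral walks are described as a test: "DBS RIGHT Only (CnF L off/CnF R on), and DBS LEFT only (CnF L on/CnF R off", alongside both-on and both-off, over a 25-foot path, each condition done twice.
- **Table 1.** Gait kinematics is marked at Visit 2 (baseline, before implantation) and Visit 9 (week 25). The velocity test is marked at Visit 2 and Visits 5 to 8, and not at Visit 9.

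**The concern.** The velocity analysis needs two conditions, left only and right only, that the article does not describe at the visits where the analysis is to be run. It cannot be carried out as written on the clinic assessments as described.

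If the text stays as it is, the analyst must either drop the planned test or choose a replacement once data are in hand, or staff must decide visit by visit whether to add unilateral walks. With four patients, an unplanned choice of contrast, or conditions recorded for some patients and visits but not others, could change what the velocity data appear to show. Velocity is one of the outcomes from which the trial intends to read a trend toward efficacy in support of a larger study.

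**Working it through.** The article gives no number of comparisons and no power calculation for this analysis, so there is no figure to reproduce. The check is a count of what the analysis needs against what the assessments describe.

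**Inputs**
- Configurations in the velocity ANOVA: 4 (Data analysis).
- Stimulation states described at clinic gait tests: 2, on and off (Study design and overview).
- Post-implantation clinic gait visits: 4, at weeks 2, 6, 12 and 24 (Study design and overview; Table 1, Visits 5 to 8).
- Configurations described at Visit 9: 4 (Kinematic and EMG evaluation of gait; Table 1).
- Patients: 4 (Participants).

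**Pairs per visit**
- Planned Tukey pairs: C(4,2) = 6.
- Pairs supported by on and off alone: C(2,2) = 1, both-on against both-off.

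**Pairs over the trial**

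| Visits counted | Planned | With described data | Without |
|---|---|---|---|
| Weeks 2, 6, 12, 24 | 4 × 6 = 24 | 4 × 1 = 4 | 20 (20/24 = 83%) |
| The same plus week 25 | 5 × 6 = 30 | 4 + 6 = 10 | 20 (20/30 = 67%) |

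**Patient-by-configuration velocity values**
- Weeks 2 to 24: 4 patients × 4 configurations × 4 visits = 64 needed; 4 × 2 × 4 = 32 described.
- With week 25: 4 × 4 × 5 = 80 needed; 32 + 4 × 4 = 48 described.

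**Can the timing be read as week 25?** No. The adjacent EMG sentence assigns its own four-configuration comparison to the final assessment, so the authors separated the two timings. Nor can Visit 9 stand in for the earlier visits: its velocity would come from a 25-foot walk, whereas clinic velocity comes from a 2-minute walk.

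**Model.** Every patient supplies every configuration. At one visit with all four configurations there are 4 × 4 = 16 values. An ordinary one-way ANOVA treats them as independent, with 16 − 4 = 12 error degrees of freedom, and leaves differences between patients in the error term. A repeated-measures model removes those differences, with (4 − 1) × (4 − 1) = 9 error degrees of freedom. The Data analysis section already uses repeated measures for UPDRS III and the questionnaires, but does not name it for the configuration comparisons.

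**The case against.** The strongest reply is that no sentence says clinic visits test on and off and nothing else. The article sometimes uses two-state wording where four configurations are meant. The kinematic section opens by speaking of walking with and without stimulation and then lists four conditions. The EMG secondary outcome is worded as on against off, yet Data analysis compares it across four configurations. The two-state wording of the velocity outcome therefore cannot show that unilateral walks are excluded. Programming also takes place at the clinic visits, so unilateral walks there are plausible, and a journal article may leave visit-level test conditions to the full protocol, which is not shown.

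This stands as far as it goes. A reader might infer that the unilateral data will not exist. The article does not support that; it supports only that no such data are described. The conflict remains, because the Study design and Assessments sections, the two-state blinding and the Data analysis section are all present and do not fit together.

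Two further inferences should be resisted. One is that this undermines the trial's main result. The stated primary goal is safety and feasibility, and no safety endpoint or stoppage rule depends on this ANOVA. The other is that extra walks would tire patients and distort the on/off contrast. The article gives no walk count, rest interval or test order for clinic visits, so this cannot be assessed and nothing here rests on it.

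**Conclusion.** The inconsistency is real and of moderate severity. On the assessments as described, 5 of every 6 planned pairwise velocity comparisons at the clinic visits have no described data: 20 of 24 over weeks 2 to 24, or 20 of 30 if Visit 9 is counted as a clinic visit. At Visit 9 itself all 6 pairs are supported.

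The counts rest on one assumption, that the two-state description of the clinic gait tests is complete. If the full protocol schedules unilateral walks at those visits, the missing comparisons disappear. The article's sections would still need to be aligned, and the one-way model would still be the wrong choice for configurations measured in the same patients.

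**What to change.** State which configurations are tested at weeks 2, 6, 12 and 24, and bring Study design and overview, Assessments, Secondary outcomes, Kinematic and EMG evaluation of gait, and Data analysis into line.

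**If clinic visits test on and off:**
- Weeks 2, 6, 12 and 24: analyse 2-minute-walk velocity as the within-patient difference, DBS on minus DBS off.
- Visit 9 only: compare 25-foot-walk velocity and EMG amplitude across the four configurations with a repeated-measures model instead of one-way ANOVA. Keep this velocity separate from the 2-minute-walk measure.

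This uses data already described and costs only wording.

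**If unilateral walks at clinic visits are intended:** say so in Study design and overview and in Assessments, extend the blinding description to four conditions, and use the same within-patient model at each visit. This adds 2 conditions × 4 visits = 8 tested conditions per patient, or 64 − 32 = 32 over four patients, relative to what is now described.

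Either choice should be fixed before the velocity data are analysed.

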### Rationale for DBS of the mesencephalic locomotor region

The mesencephalic locomotor region (MLR) is a physiologically defined area in the midbrain tegmentum, where electrical stimulation was found to initiate locomotion in cats [16, 17]. Since its discovery in 1966, the MLR has been identified in multiple species, as a phylogenetically preserved node in the supraspinal locomotor network [18–23], with studies suggesting therapeutic potential in animal models of gait disorders [24–26]. Electrophysiological and functional imaging evidence also supported its existence in humans [27–29], encouraging clinical interest in the region as a DBS target to promote gait. Specifically, this was thought to be a potential treatment for patients with the PIGD subtype of PD [15] and FOG that did not respond to levodopa therapy or conventional DBS of the STN or GPi [30–32].

Over the past 15 years, several centers have reported on DBS of the pedunculopontine nucleus (PPN), a putative anatomical component of the MLR, for postural instability and gait dysfunction in PD [33]. Despite initially promising case reports [34, 35], the efficacy of this therapy has since been called into dispute through the results of double-blinded studies and meta-analyses [36–39].

Several reasons have been posited to explain this lack of efficacy, including potential species differences in MLR function, and the degeneration of MLR neurons in PD [40–42]. A recent clinical study of DBS assessed FOG outcomes using a responder analysis. Of the reported subjects, there was a “good responder” cluster with near resolution of percent time spent in FOG with DBS on compared to off (34.1 ±14% vs. 2.7 ±2.6%) [43]. The best responders had active electrodes in the dorsal part of the MLR in the cuneiform nucleus (CnF) rather than the PPN (Fig. 1) [43]. This aligns with recent optogenetic studies in rodents, which showed that stimulation of glutamatergic neurons in the CnF effectively and specifically caused locomotor initiation [47, 48] (For review see [46]). It also agrees with preclinical electrophysiological studies in the cat, where stimulation of low threshold sites within the MLR primarily showed CnF neuron activation [49]. The importance of electrode targeting on efficacy in this region is reinforced by computer modeling studies, demonstrating that targeting errors of 1 mm can significantly decrease target activation selectivity [50].

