### Participants

We are actively screening and recruiting patients for this study from the Movement Disorders Clinic at the University of Miami Hospital. As this is a pilot study, we plan to enroll 4 patients with PD with levodopa-resistant FOG. A movement disorder neurologist will assess the eligibility of a patient based on the inclusion and exclusion criteria are detailed below.

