## Discussion

PD patients with FOG that is refractory to dopaminergic therapy have limited therapeutic options. Our study protocol aims to test the safety, feasibility, and preliminary efficacy of a novel brainstem target to alleviate FOG. Our strategy is based on a careful revisiting of classical animal studies [16], newly emerging optogenetics data [47], and a recent clinical study [43], all of which suggest that optimizing the location of DBS within the MLR could significantly improve the effect of DBS on this gait network. While some have pointed to the inconsistent outcomes of previous PPN DBS studies as a reason to abandon this approach altogether [41], that subsets of patients with FOG show significant improvement with DBS in this region suggests that refinement of methodology may be important. Through this and future larger scale studies, we hope to determine if CnF DBS could be an effective therapy for FOG and gait dysfunction in other neurodegenerative disorders.

A strength of this study is the novel use of directional electrodes to deliver DBS to this midbrain region. As a complex area comprised of numerous interleaving fiber tracts and structures, the ability to steer current would be important in optimizing therapeutic effects while mitigating stimulation-induced side effects. Limitations of this study include the small sample size, given the preliminary nature of this study, and the lack of a control cohort. Additionally, as some patients with DBS in this region feel mild paresthesias with stimulation, complete double blinding of DBS status during gait assessments may be impossible. Finally, there are limitations related to the studying of FOG itself, including potential heterogeneity of pathobiology, and difficulty in eliciting FOG in the clinical setting. We hope to mitigate these difficulties through our rigorous inclusion/exclusion criteria, and by using known triggers for FOG during gait assessments, if necessary.

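### Gait velocity is tested visit by visit with an ANOVA that has no patient term, and no stated analysis combines each patient's repeated on/off comparisons

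*Protocol article*

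**What the plan says.** All statements are in the protocol article.

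- **Sample** (Participants): "we plan to enroll 4 patients with PD with levodopa-resistant FOG".
- **Visits** (Study design and overview): subjects "will undergo repeated gait assessments in the clinic at 2-, 6-, 12-, and 24-weeks post implantation".
- **Conditions** (same section): "Gait assessment tests will be performed on medication, with DBS on and off". Each patient therefore supplies an on/off pair at each of four visits.
- **Velocity test** (Data analysis): "One-way ANOVA will be used to compare percent improvement in gait velocity for the four different DBS configurations", carried out "at each clinic visit, with the Tukey Honest Significant Difference post hoc test to compare configurations".
- **Other outcomes** (same paragraph): "One-way ANOVA with repeated measures will be used to compare changes in the UPDRS III, FOG Questionnaire, PDQ-39, and PDQL". Velocity is not in that list.

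The Secondary outcomes section puts velocity on a percent-change scale without stating the reference value. Table 1 lists programming at every follow-up visit.

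**The concern.** A one-way ANOVA treats the four configurations at a visit as four independent groups. Here they are the same four people. Without a patient term, stable differences in walking speed between patients go into the error. Because the test is run afresh at each visit, a patient's repeated on/off comparisons are never brought together in any stated analysis.

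Two things are at stake. The group estimate of the on/off effect is usually less precise than the data allow. And with one pair per visit, no patient's change can be set against that patient's walk-to-walk noise. In a four-patient pilot meant to inform a larger trial, individual effects with their error, and their spread between patients, are among the most useful things to hand on.

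**Working it through.** **Inputs.** From the article: 4 patients; 4 configurations; on/off pairs at weeks 2, 6, 12 and 24; one-way ANOVA with Tukey at each visit. It states no SD, effect size, alpha or interval width, so there is no figure to reproduce. Assumed: two-sided 5%; s = SD of one walk; tau = SD between patients of the true on/off effect, 0 to 2s; ICC = patient share of the patient-plus-walk variance, 0 or 0.7 for illustration.

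**1. Paired benchmark: one visit against three visits.** The variance of a patient's on/off difference is tau² + 2s² at one visit, and tau² + 2s²/3 for the mean of three. The 95% half-width for the group mean is 3.182 × sqrt(variance/4), with t on 3 df.

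| tau | one visit | mean of three | narrower by |
|---|---|---|---|
| 0 | 2.25s | 1.30s | 42% |
| 0.5s | 2.39s | 1.52s | 36% |
| 1s | 2.76s | 2.05s | 25% |
| 2s | 3.90s | 3.44s | 12% |

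This isolates the gain from averaging visits. It is not the loss from the plan, because the plan does not use a paired one-visit analysis.

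**2. The planned test.** With 16 values per visit and 12 error df, the half-width for bilateral-on against off is m × sqrt(MSE × 2/4). Here MSE = s²/(1 − ICC) + tau²/2, and m = 2.969 with Tukey or 2.179 unadjusted.

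| ICC | tau | planned, Tukey | planned, unadjusted | mean of three visits |
|---|---|---|---|---|
| 0 | 0 | 2.10s | 1.54s | 1.30s |
| 0 | 1s | 2.57s | 1.89s | 2.05s |
| 0 | 2s | 3.64s | 2.67s | 3.44s |
| 0.7 | 0 | 3.83s | 2.81s | 1.30s |
| 0.7 | 1s | 4.11s | 3.02s | 2.05s |
| 0.7 | 2s | 4.85s | 3.56s | 3.44s |

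For example, at ICC 0.7 and tau 0: MSE = s²/0.3 = 3.33s², and 2.969 × sqrt(1.667) × s = 3.83s. With strong patient correlation the planned comparison can be almost three times as wide (3.83/1.30 = 2.9). With none and a large tau, the gain is negligible under Tukey (3.64/3.44 = 1.06). Unadjusted, it disappears or reverses, because 12 error df replace 3.

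Over ICC 0 to 0.9 and tau 0 to 1s, with all four visits averaged, the planned half-width was 1.3 to 5.9 times the within-patient one with Tukey, and 0.97 to 4.3 times without. These ratios combine unmodelled pairing, the loss of visits and, in the first range, the Tukey multiplier.

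**3. If percent improvement is taken against the patient's own off walk.** Patient level then largely drops out, but every off value is exactly 0. Writing V for the variance of the on/off change, MSE averages three groups with variance V and one with none, so it is 0.75V. The ANOVA standard error is sqrt(0.75V × 2/4) = sqrt(0.375V) against the correct sqrt(V/4), a ratio of 1.22. The test is still mis-specified, but by less.

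**4. One patient's effect.** One pair leaves 0 df for error. Three pairs in each of four patients give 4 × (3 − 1) = 8 pooled df, so the half-width is 2.306 × sqrt(2/3) × s = 1.88s. If the true effect also varies between visits with SD s, the variance of the mean is (2s² + s²)/3 = s² and the half-width is 2.31s.

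**The case against.** The strongest case for leaving the plan alone is that visits are not replicates. Settings may change at every follow-up, and the DBS programming section itself raises habituation and waning. Analysing each visit separately is a reasonable response to that, and an average could hide drift. This stands as a caution: the per-patient interval in step 4 mixes walk noise with true change. It does not justify dropping the patient term within a visit, nor never combining visits when per-visit values can be shown beside the average.

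It is also fair that the analysis is a secondary look at trend, that group inference stays at 3 df after any repair, and that a fuller document may add summaries. But the article fixes the velocity test in words and names repeated measures for other outcomes in the same paragraph, so this is a stated choice, not mere silence.

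Some stronger readings are not supported:

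- A reader might take 12% to 42% as the loss from the planned ANOVA. It is measured against a paired analysis that the plan does not use.
- A reader might infer that the plan must identify velocity responders, since the Rationale says "A recent clinical study of DBS assessed FOG outcomes using a responder analysis" and the Discussion notes "that subsets of patients with FOG show significant improvement with DBS in this region". The cited result concerned percent time in FOG, and the Discussion speaks of improvement generally. Neither sets velocity as the responder measure.
- A reader might suppose that stimulation is established from week 6. The article says only that it begins at 2 weeks.
- A reader might say that all within-patient information is thrown away. The Safety and feasibility section promises descriptive within-subject trends, and the laboratory session repeats each condition twice, though the repeats are averaged.
- The article promises no confidence intervals. The widths above are those implied by its comparisons.

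**Conclusion.** The point holds in limited form. The stated velocity test omits the patient, so it ignores the pairing, and no stated analysis combines a patient's on/off comparisons across visits. In most scenarios the efficacy trend is less precise than the data permit, and no patient's effect has an error estimate. The direction is firm unless patient correlation is near zero and the true effect varies widely between patients. The size cannot be fixed, because it rests on assumed s, tau and ICC and on the undefined percent reference. The firmest gain is per patient: from no error estimate to one on 8 pooled df. This is a cheap improvement to a secondary, exploratory analysis. The primary safety and feasibility endpoints are not affected.

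**What to change.** Reword the velocity analysis in the Data analysis section:

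1. Compute each patient's bilateral-on versus off change at every post-implantation clinic visit, on the protocol's percent scale with the reference stated, or on log velocity.
2. Report each patient's mean over weeks 6, 12 and 24 with an interval from the pooled within-patient error.
3. Report the mean of the four patient effects with a t-interval on 3 df.
4. Show week 2, when stimulation first starts, separately.
5. Keep the per-visit values for each patient and report the week-6 to week-24 slope, so that waning or drift is visible.

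The on/off contrast exists whether clinic visits test two conditions (Study design and overview) or four (Data analysis), but those two statements should be reconciled.

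The cost is analysis wording only, with no new data or visits. The downside is that the average spans changing programming settings, so the per-patient interval includes true drift as well as walk noise. Inference beyond these patients still rests on four people.

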### Secondary outcomes

Percent change in FOG Questionnaire (FOGQ), Parkinson’s Disease Questionnaire (PDQ-39), and the Parkinson’s Disease Quality of Life Questionnaire (PDQL)Percent change in Movement Disorders Society Unified Parkinson’s Disease Rating Scale (MDS-UPDRS) Part III across study visits relative to pre-operative baseline evaluation.Percent change in number of falls (between baseline and final gait testing sessions, and on item 13 of UPDRS III)Percent change in gait velocity with and without CnF DBSPercent change in muscle electromyogram (EMG) amplitude during gait testing at study conclusion between CnF DBS on and off conditions

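### The repeated-measures ANOVA named for UPDRS III, FOGQ, PDQ-39 and PDQL does not target change from pre-operative baseline, and the role of the 2-week visit is left open

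*Protocol article*

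**What the plan says.** **Outcome.** Secondary outcomes in the protocol article lists percent change in FOGQ, PDQ-39 and PDQL, with no reference visit written for that item. It lists percent change in MDS-UPDRS Part III "across study visits relative to pre-operative baseline evaluation".

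**Analysis.** Data analysis states "One-way ANOVA with repeated measures will be used to compare changes in the UPDRS III, FOG Questionnaire, PDQ-39, and PDQL", and the end of that sentence reads "FOG Questionnaire, PDQ-39, and PDQL over the multiple time points of the study". It does not say whether baseline is one of the levels. It names no contrast against baseline, no test against zero and no post hoc procedure for these scales. Tukey's test appears in the same paragraph, but only for the comparison of stimulation configurations.

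**Timing.** Study design and overview says "all subjects will receive active stimulation beginning at 2 weeks post-implantation", with "repeated gait assessments in the clinic at 2-, 6-, 12-, and 24-weeks post implantation". Table 1 marks MDS-UPDRS, FOGQ, PDQ-39 and PDQL at the baseline visit and at the 2-, 6-, 12- and 24-week visits, and also marks programming at the 2-week visit. The order of scales and switch-on at that visit is not given.

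**Size and role.** Participants says "we plan to enroll 4 patients with PD with levodopa-resistant FOG". Data analysis presents the secondary outcomes as a look for a trend toward efficacy; the primary aim is safety and feasibility.

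**The concern.** The outcome asks how far each patient has moved from the pre-operative state. A one-way repeated-measures ANOVA asks whether the visit means are all equal. The two questions coincide only in part, and how far depends on a choice that the article does not state: whether baseline is one of the visits compared.

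The 2-week visit raises a second, separate question. A questionnaire about recent daily life completed on the day stimulation begins may cover little or no stimulated time, and the patient is then two weeks past brain surgery. A shift at that visit is not evidence about stimulation, yet it would contribute to a time effect.

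At stake is the efficacy signal from these scales. The article says the pilot is meant to support larger trials, and their planners need an estimated change with its uncertainty. A p-value for some difference among visits does not supply that.

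**Working it through.** The article gives no power, alpha or effect size for these scales, so there is no figure to reproduce.

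**Inputs from the article.** n = 4; follow-up at weeks 2, 6, 12 and 24; one pre-operative baseline.

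**Assumptions.** Two-sided alpha 0.05; benefit d in SDs of the raw score; equal correlation rho between visits, 0.3 to 0.8.

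**Formulas.** For the ANOVA with k visits, df = k−1 and 3(k−1), and noncentrality λ = n·Σ(μj − μ̄)² / (1 − rho). For the contrast mean of weeks 6, 12 and 24 minus baseline, SE = √[(1 − rho)(1 + 1/3)/4], tested as a paired t on 3 df.

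**Reading A: levels are the four changes from baseline (df 3 and 9).** With a benefit of d at all four visits, every deviation from the mean is 0, so λ = 0. The rejection rate is 0.05 for every d and rho. Simulation (40,000 runs, rho 0.7) gave 0.051 at d = 1 and 0.050 at d = 2.

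**Reading B: baseline is a level (df 4 and 12).** Means 0, 1, 1, 1, 1 have mean 0.8, so Σ = 0.64 + 4 × 0.04 = 0.80. At rho 0.7, λ = 4 × 0.80 / 0.3 = 10.7 and power is 0.56.

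**No effect at week 2, then a benefit of 1 SD.**
- Reading A: means 0, 1, 1, 1 give Σ = 0.5625 + 3 × 0.0625 = 0.75; λ = 10.0 and power 0.56 at rho 0.7.
- Reading B: means 0, 0, 1, 1, 1 give Σ = 2 × 0.36 + 3 × 0.16 = 1.20; λ = 16.0 and power 0.76.

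Power at d = 1:

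| rho | A, steady | B, steady | A, none at week 2 | B, none at week 2 | Contrast, 3 df |
|---|---|---|---|---|---|
| 0.3 | 0.05 | 0.26 | 0.26 | 0.38 | 0.31 |
| 0.5 | 0.05 | 0.35 | 0.36 | 0.51 | 0.40 |
| 0.7 | 0.05 | 0.56 | 0.56 | 0.76 | 0.57 |
| 0.8 | 0.05 | 0.76 | 0.75 | 0.91 | 0.73 |

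The contrast does not use week 2, so its power is the same in both scenarios.

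**What the F cannot tell apart.** Under Reading B, a 1-SD shift at week 2 only (0, 1, 0, 0, 0) has mean 0.2 and Σ = 0.64 + 4 × 0.04 = 0.80, the same as the sustained benefit. Power is therefore identical (0.56 at rho 0.7). Under Reading A, a shift at week 2 only (1, 0, 0, 0) gives Σ = 0.75, the same as a benefit starting at week 6. Because the deviations are squared, worsening counts the same as improvement.

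**Dilution by week 2.** If week 2 carries no effect, the mean of all four follow-ups minus baseline is 0.75 d. At d = 1 and rho 0.7, the contrast that omits week 2 has 1/√(0.3 × 1.333/4) = 3.16 and power 0.57. With week 2 included, 0.75/√(0.3 × 1.25/4) = 2.45 and power is 0.40.

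**Sphericity.** Five visits give four contrasts. With 4 patients their sample covariance has rank at most 3, so a formal sphericity test is not possible. Under first-order serial correlation of 0.6 to 0.9 between successive visits and no effect, the uncorrected five-visit F rejects in roughly 7% to 9% of simulated trials. Under Reading A there are three contrasts, and the rank argument does not apply.

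**The case against.** The strongest objection is that the time points include baseline, since Table 1 schedules all four scales there. On that reading the F does respond to a steady benefit, and a flat statement that the analysis cannot detect change from baseline would be wrong. This stands: the text permits both readings, and the 5% result belongs to Reading A only.

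A reader might also infer that counting week 2 as follow-up is why a steady benefit would be missed. The figures point the other way. If week 2 carries no effect, the profile is no longer flat and a later benefit becomes more visible to the ANOVA (0.05 to 0.56 under Reading A, 0.56 to 0.76 under Reading B, at d = 1 and rho 0.7). Nor does the article say that week 2 enters the ANOVA as an on-treatment visit, or that its scales precede switch-on; both would be inferences from the schedule. UPDRS III is examiner-rated and could be scored with stimulation on.

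The contrast should not be sold on power. With pooled error on 12 df it reaches about 0.82 at d = 1 and rho 0.7, but that relies on the sphericity that cannot be tested. On 3 df it reaches 0.57, level with the five-visit F for a steady benefit and below that test's 0.76 if week 2 shows no effect.

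The sphericity point is modest too: a Greenhouse-Geisser correction can still be computed, and the inflation is small for an exploratory analysis.

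Finally, contrasts and intervals are often left to a fuller document, and the percent changes are themselves effect estimates. That limits the weight. The point remains because the article names a specific test, and under neither reading does it target the outcome that the article defines.

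**Conclusion.** The point holds in limited form. The named omnibus test does not target the stated outcome. If post-baseline changes are compared, a constant benefit is found only at the alpha rate. If baseline is a level, power for a steady 1-SD benefit is about 0.26 to 0.76, but the result has no direction or interval and is not specific to change from baseline.

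The 2-week visit is a separate issue of dilution and attribution. It can pull down an average follow-up effect, and a post-surgical shift there alone could yield a significant time effect.

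The power figures rest on the assumed alpha, effect size and equal correlation between visits. The zero noncentrality for a flat profile of changes does not depend on effect size or correlation. No trial decision hangs on these p-values, so this is worth correcting but does not threaten the primary aim.

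**What to change.** For each of the four scales, pre-specify one contrast: the mean of weeks 6, 12 and 24 minus pre-operative baseline, with its estimate and 95% confidence interval from the four patient-level differences (paired, 3 df). Show all four individual trajectories. Report week 2 separately, and state whether its scales were completed before or after stimulation was switched on. If the ANOVA is kept as a supplement, state whether baseline is a level.

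The cost is about one sentence of analysis text and a note on the order of tasks at the 2-week visit; no visits or patients are added. The price is a wide interval. At rho 0.7 the half-width is about 3.18 × √(0.3 × 1.333/4) = 3.18 × 0.316 ≈ 1.0 SD. It is about 1.5 SD at rho 0.3 and 0.8 SD at rho 0.8. The result stays exploratory, and the interval shows plainly how little four patients can settle.
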